
#### Transcutaneous spinal cord stimulation protocol

2.5.2

Both groups will receive identical tSCS protocols. Stimulation will be delivered using the ARC-EX™ transcutaneous spinal cord stimulation system (ONWARD Medical, Lausanne, Switzerland) through adhesive surface electrodes positioned over the spinous process. The ARC-EX™ device has been registered with the Health Sciences Authority (HSA), Singapore, under Class B medical device notification (CRM-N) for research purposes only. A single cathode electrode (5 cm × 10 cm) will be placed midline over the spinous processes at the vertebral level corresponding to the lumbosacral enlargement (typically T11–L1), consistent with published tSCS configurations for lower limb targeting (Hofstoetter et al., 2018). Two anode electrodes (5 cm × 5 cm each) will be placed bilaterally over the iliac crests.

Stimulation will be delivered as biphasic rectangular pulses at a frequency of 30 Hz, which has been shown to effectively modulate spinal motor circuits (Hofstoetter et al., 2018). The pulse width will be set at 1 ms. Stimulation intensity will be individualized for each participant. The sensory threshold will be defined as the lowest intensity at which the participant reports a tingling or vibrating sensation directly beneath the tSCS electrode on the skin surface. This refers to cutaneous sensation at the electrode site and not referred sensation into the lower limb dermatomes. The motor threshold will be defined as the lowest intensity at which a visible involuntary muscle twitch is observed in the lower extremities. These thresholds will be determined by incrementally increasing stimulation intensity from subthreshold levels. The target tSCS intensity will be set at the highest tolerable level below motor threshold that does not elicit involuntary muscle contractions, typically 40–100 mA depending on individual sensitivity and electrode impedance.

Each tSCS session will last 45 min. During tSCS, participants will engage in structured, task-specific lower limb rehabilitation activities. These may include overground walking practice (with or without assistive devices), standing balance exercises, sit-to-stand transfers, and lower limb strengthening exercises, supervised by a qualified physiotherapist. Activities will be selected and progressed based on the participant's functional level and treatment goals. It is acknowledged that the tSCS electrode configuration and stimulator cables may limit the range of movement-based activities; therefore, therapy tasks will be adapted to accommodate equipment constraints while maximizing active participation. Stimulation parameters (intensity, electrode impedance) will be monitored throughout each session, and adjustments will be made as needed to maintain optimal stimulation delivery.

#### Combined intervention schedule

2.5.3

Treatment sessions will be conducted on 2 non-consecutive fixed days per week (e.g., Monday and Thursday, or Tuesday and Friday), selected at enrolment based on participant and therapist availability and maintained consistently throughout the 16-week intervention period (32 sessions total). Fixed scheduling was chosen to ensure consistent inter-session intervals for neuroplastic consolidation. Each session will begin with the tSCS (45 min) paired with therapy and followed by the TMS protocol (approximately 3–4 min for iTBS). The temporal proximity of TMS and tSCS is designed to leverage potential synergistic effects of cortical and spinal neuromodulation within overlapping windows of enhanced plasticity.

Sessions will be scheduled with a minimum of 24 h between sessions to allow for neuroplastic consolidation effects and to minimize participant burden. Participants who miss scheduled sessions will be offered make-up sessions within the same week when possible. A minimum attendance rate of 90% (29/32 sessions) will be required for inclusion in the per-protocol analysis.

### Concomitant care

2.6

Participants will be encouraged to continue their usual rehabilitation activities and physical therapy throughout the study period. To minimize confounding, participants will be asked not to initiate, discontinue, or alter the dose of medications likely to influence outcomes of interest, particularly anti-spasticity agents, anticonvulsants, and centrally acting drugs, unless a change is clinically required. Participants will not be asked to modify any pre-existing medication regimen as a condition of enrolment. Any medication changes occurring during the study will be documented and accounted for in sensitivity analyses. Any changes to medications or rehabilitation programs will be documented and considered in sensitivity analyses. Participants will not be permitted to enroll in other interventional trials or initiate new neuromodulation treatments during the study period.

### Study schedule

2.7

See Table 2 in study schedule.

**Table 2 T2:** Schedule of enrollment, interventions, and assessments.

Assessment/activity	Screening	Baseline	Week 8	Week 16	Week 20	Ongoing
Informed consent	X					
Eligibility assessment	X					
Medical history	X					
Randomization		X				
tSCS + sham TMS (control group)						2x/week
tSCS + active iTBS TMS (intervention group)						2x/week
ISNCSCI/LEMS		X	X	X	X	
10MWT/6MWT		X	X	X	X	
SCIM-III		X	X	X	X	
Modified Ashworth scale		X	X	X	X	
Electromyography		X	X	X	X	
MEP assessment		X		X	X	
Adverse event monitoring						Each visit

ISNCSCI, International Standards for Neurological Classification of Spinal Cord Injury; LEMS, Lower Extremity Motor Score; 10MWT, 10-Meter Walk Test; 6MWT, 6-Minute Walk Test; SCIM-III, Spinal Cord Independence Measure-III; MEP, Motor Evoked Potential.

## Outcome measures

3

### Primary outcome

3.1

The primary outcome measure is change in Lower Extremity Motor Score (LEMS) from baseline to Week 16, the immediate post-intervention timepoint (Table 3). Week 16 was selected as the primary endpoint because it captures the maximal cumulative effect of the combined neuromodulation protocol following completion of all 32 sessions, aligns with established convention in TMS and tSCS rehabilitation trials (Benito et al., 2012; Kumru et al., 2016; Feng et al., 2023; Shi et al., 2025), and minimizes confounding from post-intervention behavioral variability (e.g., changes in physical activity or unsupervised practice) that may differentially affect the two arms during follow-up. Week 20 is retained as a pre-specified secondary time-point to assess durability of treatment effects within the MMRM framework (Section 5.3).

**Table 3 T3:** Summary of outcome measures.

Outcome	Type	Measurement tool	Clinical significance
Lower extremity motor score	Primary	ISNCSCI (0–50 points)	MCID: 2–3 points; predicts ambulation
Walking speed	Secondary	10MWT (m/s)	MCID: 0.15 m/s
Walking endurance	Secondary	6MWT (meters)	MCD: 45.8 meters; MCID estimates range 30–50 meters
Functional independence	Secondary	SCIM-III (0–100)	Comprehensive SCI-specific measure
Quality of life	Secondary	EQ-5D-5L	Health utility index and EQ-VAS; validated in SCI populations
Spasticity	Secondary	Modified Ashworth Scale (0–4)	Clinician-rated muscle tone
Corticospinal excitability	Exploratory	MEP amplitude/latency	Neurophysiological plasticity marker
EMG	Exploratory	EMG activity	Muscle activity/recruitment

ISNCSCI, International Standards for Neurological Classification of Spinal Cord Injury; 10MWT, 10-Meter Walk Test; 6MWT, 6-Minute Walk Test; SCIM-III, Spinal Cord Independence Measure-III; MEP, Motor Evoked Potential; MCID, Minimal Clinically Important Difference.

The LEMS is a component of the International Standards for Neurological Classification of Spinal Cord Injury (ISNCSCI), representing the summed strength of five key muscle groups in each lower extremity (hip flexors, knee extensors, ankle dorsiflexors, great toe extensors, and ankle plantarflexors), graded on a 0–5 scale for each muscle group. The total LEMS ranges from 0 to 50 points, with higher scores indicating greater motor strength (Kirshblum et al., 2011).

The LEMS is a well-established measure of lower extremity motor function in SCI populations, assessed as part of the ISNCSCI examination and standardised across clinical settings (Kirshblum et al., 2011). Importantly, LEMS has been shown to be a strong predictor of ambulatory capacity and functional independence following SCI (Ditunno et al., 2007). LEMS improvements have been associated with meaningful functional gains in chronic iSCI populations, though establishing definitive minimal clinically important difference thresholds remains an area of ongoing investigation (Wu et al., 2015). The measure's strong correlation with walking ability and independence outcomes makes it particularly valuable for assessing motor recovery interventions.

### Secondary outcomes

3.2

All secondary outcomes will be assessed at baseline, Week 8, Week 16, and Week 20, with the exception of MEP assessments, which will be conducted at baseline, Week 16 and Week 20 only, as shown in Table 2.

**Walking Function:** The 10-Meter Walk Test (10MWT) will assess walking speed over a 10-meter distance at both comfortable and maximum speeds, with excellent reliability (inter-rater *r* = 0.97, intra-rater *r* = 0.98) established for SCI populations (Jackson et al., 2008). The 6-Minute Walk Test (6MWT) will measure walking endurance as the total distance walked in 6 min on a standardized course (Lam et al., 2008). The type and level of assistive device used during baseline assessment of the 10MWT and 6MWT (e.g., rolling walker, forearm crutches, cane, or no device) will be documented and standardized across all subsequent assessment time points to ensure reproducibility and valid within-participant comparisons.

**Functional Independence:** The Spinal Cord Independence Measure-III (SCIM-III) is a disability scale specifically developed for persons with SCI, assessing self-care (0–20 points), respiration and sphincter management (0–40 points), and mobility (0–40 points). The total score ranges from 0 to 100, with higher scores indicating greater independence (Catz et al., 2007).

**Quality of Life:** The EQ-5D-5L (EuroQol Group) will be administered to capture participant-perceived health status across five dimensions: mobility, self-care, usual activities, pain/discomfort, and anxiety/depression, along with a visual analog scale (EQ-VAS) for overall health. The EQ-5D-5L is widely validated in SCI populations, is brief to administer, and generates utility values that can support future health economic evaluations of the intervention (Herdman et al., 2011).

**Spasticity:** The Modified Ashworth Scale (MAS) will be used to assess spasticity in bilateral hip flexors, knee extensors, and ankle plantarflexors, graded from 0 (no increase in tone) to 4 (limb rigid in flexion or extension).

**Neurophysiological Measures:** Motor evoked potentials (MEPs) will be recorded from the tibialis anterior and soleus muscles bilaterally in response to single-pulse TMS over the motor cortex. MEP amplitude (peak-to-peak), MEP latency, and cortical silent period duration will be measured to characterize corticospinal excitability and inhibitory function. Additionally, recruitment curves will be constructed by delivering TMS at intensities ranging from 100% to 150% of motor threshold to assess the input-output properties of corticospinal projections (Rossini et al., 2015).

Motor threshold for neurophysiological assessments is defined as the minimum TMS intensity required to elicit MEPs of ≥50 μV peak-to-peak amplitude in at least 5 out of 10 consecutive trials in the target muscle at rest (resting motor threshold, RMT) or during slight voluntary contraction (active motor threshold, AMT).

**Electromyography (EMG):** Surface electromyography (EMG) will be recorded bilaterally from the tibialis anterior, medial gastrocnemius, rectus femoris, and biceps femoris muscles. Bipolar Ag/AgCl surface electrodes will be placed over the muscle belly in accordance with SENIAM guidelines, with an inter-electrode distance of 20 mm (Hermens et al., 2000). A reference electrode will be placed on the ipsilateral fibular head. Signals will be amplified (gain × 1,000), bandpass filtered (20–500 Hz), and sampled at 2,000 Hz. Data will be acquired using the Noraxon Ultium EMG wireless surface EMG system (Noraxon USA Inc., Scottsdale, AZ, USA) and visualized using Noraxon MR-XP 1.07 software. EMG will be recorded during dedicated assessment sessions at baseline, Week 8, Week 16, and Week 20, and not during treatment sessions. Participants will perform three maximum voluntary isometric contractions of each recorded muscle, each held for 5 s with 60-s rest intervals, to allow normalization of EMG amplitude. Continuous lower limb EMG will also be recorded during the 10MWT at comfortable speed to characterize muscle activation timing and recruitment patterns during gait. Instructions and rest intervals will be standardized across all assessment sessions.

## Safety monitoring

4

### Adverse events

4.1

Adverse events (AEs) will be systematically monitored and documented throughout the study period. At each treatment session, participants will be asked about any symptoms or problems experienced since the last visit. All AEs will be recorded on standardized case report forms, including onset date, duration, severity (mild, moderate, and severe), relationship to study intervention (unrelated, possibly related, probably related, and definitely related), and outcome.

Anticipated adverse events associated with TMS include:

Transient headache (common, typically mild).Scalp discomfort at stimulation site.Transient tinnitus or hearing changes.Fatigue.Seizure (rare, < 0.1% with established safety guidelines).

Anticipated adverse events associated with tSCS include:

Local skin irritation at electrode sites.Transient paresthesias during stimulation.Muscle soreness or cramping.Autonomic dysreflexia (AD), a potentially serious complication in participants with injury levels at or above T6, characterized by acute hypertension, bradycardia, headache, and diaphoresis. All staff will be trained in AD recognition and emergency management, including upright positioning, removal of stimulation, identification and elimination of noxious stimuli, and administration of rapid-acting antihypertensive agents (e.g., sublingual nifedipine) as per institutional AD management protocols. Participants with injury levels at or above T6 will have blood pressure monitored at the start, during, and at the end of each session.

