**Objective:**

To evaluate the efficacy and safety of combined TMS-tSCS intervention compared to tSCS alone for improving lower extremity motor function in individuals with chronic incomplete spinal cord injury.

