### Study objectives

1.2

The primary objective of this study is to evaluate whether combined TMS-tSCS yields superior improvements in lower extremity motor function, as measured by the Lower Extremity Motor Score (LEMS), compared to tSCS alone in individuals with chronic incomplete spinal cord injury.

Secondary objectives include:

To compare changes in walking speed and endurance between treatment groups.To assess differences in functional independence outcomes between groups.To evaluate the effects of combined stimulation on spasticity.To characterize neurophysiological changes in corticospinal excitability.To assess the safety and tolerability of combined TMS-tSCS.

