### Randomization and blinding

2.4

Eligible participants will be randomized in a 1:1 ratio to the intervention or control group using a computer-generated randomization sequence with randomly permuted block sizes of 4 and 6. Randomization will be stratified by baseline LEMS (10–30 vs. 31–45) and AIS grade (C vs. D) to ensure balanced distribution of prognostic factors between groups. The randomization sequence will be generated by an independent statistician and concealed using a secure, web-based randomization system accessible only to unblinded study personnel.

Given the nature of the intervention, complete participant blinding is challenging. However, the sham TMS procedure will employ established protocols designed to minimize perceptible differences from active stimulation. A specialized sham coil that produces similar acoustic artifacts and scalp sensations without delivering effective magnetic stimulation will be used for the control group. Participants will be informed that they may receive either active or sham TMS and will be asked not to discuss their perceived treatment assignment with assessors.

All outcome assessors will be blinded to treatment allocation. Assessors will not be present during treatment sessions and will be instructed to avoid discussing treatment details with participants. At the conclusion of the study, assessor blinding will be evaluated by asking assessors to guess participants' group assignments; successful blinding will be indicated by assignment accuracy no better than chance (50%).

The TMS and tSCS interventions will be delivered by trained, unblinded research therapists who will not be involved in outcome assessments. Intervention therapists and outcome assessors will work independently, with no overlap in roles, to maintain assessor blinding.

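### Adverse events are elicited by an open question at sessions run by unblinded therapists, which leaves the between-arm comparison of subjective symptoms open to influence; a fixed-wording checklist would reduce this cheaply

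*Protocol article*

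**What the plan says.** The abstract words the aim comparatively: "To evaluate the efficacy and safety of combined TMS-tSCS intervention compared to tSCS alone". Section 1.2 lists a matching secondary objective: "To assess the safety and tolerability of combined TMS-tSCS".

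Section 4.1 fixes the occasion and form of the enquiry: "At each treatment session, participants will be asked about any symptoms or problems experienced since the last visit". Answers go on standard forms with onset, duration, severity, outcome and "relationship to study intervention (unrelated, possibly related, probably related, and definitely related"). The section then lists the events expected with TMS and with tSCS. Table 2 schedules "Adverse event monitoring" at each visit.

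Section 2.4 states who runs the sessions: "The TMS and tSCS interventions will be delivered by trained, unblinded research therapists who will not be involved in outcome assessments". The same section says of the blinded staff: "Assessors will not be present during treatment sessions and will be instructed to avoid discussing treatment details with participants".

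For serious events, Section 4.2 has the principal investigator assess causality and an independent physician verify it. Section 4.3 ties the stopping rules to the incidence of serious events.

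**The concern.** The protocol separates roles carefully for the efficacy outcomes but describes no similar protection for adverse events. The main occasions for asking about symptoms fall at sessions delivered by staff who know the arm, and the only staff stated to be blinded are not there.

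This matters because of the kind of event expected. Of the five events listed for TMS, four are symptoms that come to light mainly because someone asks: headache, scalp discomfort, tinnitus or hearing change, and fatigue. The fifth is seizure. An open question leaves the depth of follow-up to the person asking. Someone who knows the coil is sham may probe less. Someone who knows it is active may probe more, or may pass over a mild headache as expected. Either habit shifts the recorded counts in one arm, and the direction cannot be known in advance.

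At stake is the comparison of mild and moderate symptoms behind the safety and tolerability objective.

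**Working it through.** The plan gives no adverse-event rate, so there is no figure of its own to reproduce. The check has two parts.

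**1. The passages side by side**

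| Question | What the protocol article states | Where |
|---|---|---|
| Is safety compared between arms? | Yes | Abstract, Objective |
| When are events elicited? | At each treatment session; Table 2 says each visit | 4.1; Table 2 |
| Who delivers the stimulation? | Unblinded therapists | 2.4 |
| Are blinded assessors at sessions? | No | 2.4 |
| Who asks the question? | Not stated | 4.1 |
| Who rates severity and relatedness? | Not stated | 4.1 |
| Who rates causality of serious events? | Principal investigator, verified by an independent physician; masking of either not stated | 4.2 |
| Are the reporting participants masked? | Sham coil imitates sound and scalp sensation; masking called imperfect | 2.5.1; Discussion |

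The first four rows establish that per-session enquiry takes place where the arm is known to the staff delivering treatment, and that the blinded assessors cannot make it. The fifth and sixth rows limit the conclusion. The person asking could be the unblinded therapist or the physiotherapist who supervises activity during tSCS (Section 2.5.2), whose masking is not stated. The each-visit entry in Table 2 may also allow enquiry at the assessment visits, but the 32 sessions are far more numerous than the assessments at Weeks 8, 16 and 20.

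**2. Scale, on assumed rates**

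Inputs: 30 participants per arm (Section 2.3). Assumptions: a true proportion p with a given symptom, equal in both arms; all such participants recorded in the active arm; a fraction s recorded in the control arm.

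- False difference = p − p·s = p(1 − s)
- 95% half-width = 1.96 × √[p(1 − p)/30 + ps(1 − ps)/30]

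Worked case, p = 0.40 and s = 0.75: the false difference is 0.40 × 0.25 = 0.10, or 3 of 30 participants. The half-width is 1.96 × √(0.24/30 + 0.21/30) = 1.96 × √0.015 = 0.240.

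| p | s | False difference (points) | 95% half-width (points) |
|---|---|---|---|
| 0.20 | 0.90 | 2 | 19.8 |
| 0.20 | 0.75 | 5 | 19.2 |
| 0.20 | 0.50 | 10 | 17.9 |
| 0.40 | 0.90 | 4 | 24.5 |
| 0.40 | 0.75 | 10 | 24.0 |
| 0.40 | 0.50 | 20 | 22.6 |
| 0.60 | 0.90 | 6 | 25.0 |
| 0.60 | 0.75 | 15 | 25.0 |
| 0.60 | 0.50 | 30 | 24.0 |

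In every row but the last, the false difference is smaller than the half-width. If under-recording fell on the active arm instead, the sign would reverse. No figure is given for relatedness, because the article names no rater for non-serious events.

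**The case against.** The strongest reply is that most of this rests on silence. Section 4.1 is in the passive voice and names neither the person asking nor the rater. A journal article commonly leaves such detail to the full protocol, which is not shown. That stands. A reader might infer that relatedness is rated by someone who knows the arm; the document does not say so. Nor does it say that relatedness is judged against the TMS event list, or that the comparison will rest on related events. What is not silence is where the question is asked and who is kept away.

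Existing protections also count. The same question is put in both arms at every session and the answers go on standard forms. Participants are told that they may receive sham, and the sham coil produces clicks and scalp sensation. tSCS is identical in both arms. These features reduce the risk. They do not remove it: the forms standardise the record and are not said to standardise the questioning, and the Discussion concedes that participant masking is imperfect.

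Serious events depend least on how a question is worded, their causality has an independent check, and the stopping rules rest on them. The concern is therefore confined largely to milder, self-reported symptoms.

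The size is wholly assumed and mostly within sampling error at 30 per arm. That is correct. It limits the weight of the point, although a systematic shift is not made harmless by a wide interval.

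Finally, a remedy must not create new problems. A self-completed form may not suit participants with high cervical injury, whose limited hand function Section 6.2 already recognises. Passing symptom reports to outcome assessors could hint at the arm and weaken masking of LEMS. Both objections are sound and shape the fix.

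**Conclusion.** The point holds in a limited form. As described, elicitation of subjective adverse events is open to influence from knowledge of the arm, in a trial that states a comparative safety aim. This rests on stated text: the enquiry is open, it takes place at treatment sessions, those sessions are delivered by unblinded therapists, and the blinded assessors are absent.

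A reader might go further and conclude that severity and relatedness are rated unmasked, or that the safety comparison is biased. The document supports neither. It does not name the raters of non-serious events or say whether they are masked, and it gives no event rates. Over assumed true rates of 20% to 60%, with 90% to 50% of control events recorded, the false difference runs from 2 to 30 percentage points. That range shows what such a mechanism could do; it is not an estimate for this trial.

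The primary LEMS analysis is unaffected. This is a low-cost improvement to safety ascertainment, not a defect that undermines the trial.

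**What to change.** In Section 4.1, replace the open question with a symptom checklist in fixed wording. It should cover the listed TMS and tSCS events and end with one open item. Use the same list in both arms and give it before any stimulation at each session. Let participants complete it themselves, or have it read aloud word for word where hand function is limited.

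Report the between-arm comparison on all-cause events, so that it does not depend on attribution. Where an existing investigator without access to allocation is available, and is not an outcome assessor, have that person rate relatedness from the record.

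Cost: one form and a minute or two per session. The checklist itself needs no new staff. Prompted questioning will raise mild event counts in both arms, so the rates should not be compared directly with those from trials that used open questioning.
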